### Informed consent

Prior to enrollment, the trained researcher will introduce the purpose and content of this study to the qualified AMI patients as well as their families. Patients and their families will also be informed of the possible benefits and potential risks. They will have 24 h to consider whether to participate in the trial or not to ensure that patients are entirely voluntary. Furthermore, we will explain to the patients that participating or not participating in the study does not affect their normal treatment. Clues to the participant’s personal information, such as name and hospital number, will be coded instead. The personal information of all participants will always be kept confidential.

### Randomization and allocation

Eligible patients will be randomized in a 1:1 ratio to receive bifidobacteria triple viable capsule or only receive the standard treatment strategy immediately after signing the informed consent form. Randomization will be performed blockwise with variable-sized blocks. The block sizes will not be disclosed to ensure concealment. Random number tables will be generated by a study-independent staff with no other involvement in the study using the SPSS statistical software (SPSS Inc., Chicago, IL, USA, version 25). The researcher will be informed of the treatment allocation plan of the patients after sending basic information about eligible subjects to the staff of the central random system through the Internet.

### Interventions

Both groups will receive necessary treatments, such as interventional therapy/thrombolysis and medication for coronary heart disease (including but not limited to dual anti-platelet therapy, AECI/ARB, beta blockers, lipid-lowering drugs). Participants will be randomly assigned in 1:1 to either a probiotic group (bifidobacteria triple live bacteria capsules, 840 mg twice a day) or a control group (without bifidobacteria triple live bacteria capsules) during the hospitalization, for a maximum of 30 days. Each probiotic capsule contains active *Bifidobacterium longum*, *Lactobacillus acidophilu*s, and *Enterococcus faecalis*, with the concentration of each bacterium being 1 × 10^7^ CFU/210 mg. During the study period, patients or their guardians will be instructed to record their daily medication as required to ensure compliance. The drug will be discontinued when patients incur severe adverse reactions or required to withdraw from the trial. A brief overview of the study process is provided in Fig. 1. Bifidobacteria triple live bacteria capsules will be provided by Shanghai Xinyi Pharmaceutical Co., Ltd. (Shanghai, China).

**Fig. 1 Fig1:**
[figure not shown]
Participant flow diagram

### Blinding

This is an open-label trial. Trial participants, investigators, caregivers, outcome assessors, and data analysts are not blinded to the group assignment.

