## Background

Acute myocardial infarction (AMI) is a severe form of coronary heart disease, and its high morbidity and mortality pose the main threat to human life and health. The incidence of adverse cardiovascular events after AMI, such as heart failure and arrhythmias, is associated with a substantially higher risk of death [1, 2]. In recent decades, with the rise of reperfusion therapy and the standardization of treatment for AMI, the mortality rate has decreased significantly. However, a significant inpatient mortality rate remains and can be as high as 8.9% [3], and the incidence of heart failure after acute myocardial infarction during hospitalization ranged from 40.2 to 40.5% [4]. Therefore, the treatment of acute myocardial infarction needs to be further optimized.

Recent studies have shown an important link between intestinal flora and the severity of myocardial infarction and heart repair after myocardial infarction [5, 6]. Intestinal disorders and bacterial translocations play an important role in the development of myocardial infarction and in cardiovascular events after infarction [7]. Patients with acute coronary syndrome (ACS) had typical intestinal microflora disorders, which were manifested as increased harmful bacteria and decreased beneficial bacteria [8]. Many animal studies have confirmed that probiotics can reduce the size of myocardial infarction and reduce cardiac hypertrophy [5, 9]. Several clinical trials have also reported that probiotics can reduce ventricular remodeling after MI and improve ventricular systolic function in patients with heart failure [10, 11], which imply that probiotic supplementation may improve the prognosis of acute myocardial infarction. However, it has not been reported whether probiotics can reduce the incidence of adverse cardiovascular events and mortality in patients with MI in the hospital. In this study, we will evaluate the effect of probiotics on in-hospital mortality and the incidence of major adverse cardiovascular events (MACE) in patients with AMI to understand whether probiotics have a protective effect on patients with acute myocardial infarction through a randomized controlled trial (RCT).

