#### Primary outcome

The primary outcome will be in-hospital all-cause mortality at 30 days. We will keep track of each patient’s survival through telephone follow-up and the electronic medical record system, and in case of death, the cause of death will be recorded. At the end of the trial, the total number of participants, the number and proportion of deaths in the two groups will be counted, and the in-hospital mortality will be compared between the two groups.

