### Definition

In this study, MACE is defined as heart failure, malignant arrhythmias, cardiogenic shock, cardiac death, and recurrent myocardial infarction.According to the AHA/ACC/HFSA Guidelines for Managing Heart Failure [15], the diagnosis of heart failure is mainly based on clinical manifestations and physical examination: (1) typical clinical manifestations of new-onset heart failure (such as dyspnea, ankle edema, fatigue), (2) moist rales could be heard in more than one-third of the lung fields, (3) chest X-ray showed non-cardiac pulmonary edema or pulmonary obstruction, and (4) abnormal levels of brain natriuretic peptide or B-type natriuretic peptide precursor.Malignant arrhythmias are defined as atrial fibrillation/flutter, ventricular tachycardia, and high-degreee atrioventricular block.The criteria for cardiogenic shock include less than 90 mmHg systolic blood pressure, continuing for at least 30 min, clinical signs of pulmonary congestion, and organ perfusion for signs of damage to at least one of the following performance: the mental state changes, skin and limbs cold and wet, oliguria, and urinate less than 30 ml per hour.Cardiac death is defined as death from any of several cardiac causes.Recurring myocardial infarction is defined as another myocardial infarction 28 days after the onset of acute myocardial infarction, with ST-elevation ≥ 1 mm recurs, or new pathogomonic Q waves appear in at least two contiguous leads, especially when accompanied by symptoms of ischemia.Myocardial infarction-related mechanical complications include cardiac rupture, ventricular septal rupture, and papillary muscle rupture.

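### Outcome assessors and data analysts are left unblinded, which the lack of a placebo does not require; LVEF, heart failure and cardiac death are open to assessment bias, the primary outcome hardly at all

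*Protocol article*

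**What the plan says.** The Blinding section of the protocol article covers every party in one sentence: it lists patients, investigators and caregivers, and then adds that "outcome assessors, and data analysts are not blinded to the group assignment". The only reason given is that the trial is open-label. Under Interventions, the control group receives standard treatment without the capsule, and no placebo capsule is described.

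The primary outcome is death from any cause: "The primary outcome will be in-hospital all-cause mortality at 30 days". The secondary outcomes include MACE and LVEF by echocardiography at baseline, day 7 and day 30. Under Definition, "MACE is defined as heart failure, malignant arrhythmias, cardiogenic shock, cardiac death, and recurrent myocardial infarction". For the first of these components, "the diagnosis of heart failure is mainly based on clinical manifestations and physical examination"; four criteria follow, with no statement of how many must be met. For another, "Cardiac death is defined as death from any of several cardiac causes".

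Under Randomization and allocation, the researcher is told the allocation. Under Data collection and management, the researchers complete the case report forms and enter the data. The article describes no masked echocardiogram reading, masked event classification or coded arms for analysis. The independent monitoring committee reviews data and is not described as adjudicating outcomes.

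**The concern.** Without a placebo, patients and the clinicians treating them will know the arm. The person reading a stored echocardiogram, the person classifying an event from a record and the person running the analysis do not need to. The protocol puts all of them in one sentence and so gives up a protection that the open-label design leaves available.

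This matters where the outcome involves judgement. LVEF depends on a reading. Heart failure depends largely on symptoms and signs, with an unstated threshold. Cardiac death depends on attributing a cause. MACE and ventricular systolic function make up the trial's stated secondary objective, and the Discussion says the effect on prognosis will be shown through both mortality and MACE. Secondary event rates are compared by a chi-square test, so any difference between arms in how readily an event is recorded passes directly into the result.

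**Working it through.** **Planned numbers.** The Blinding section contains no figure, so the check starts from the sample size. The protocol assumes mortality of 8.9% against 5.34%, two-sided alpha 0.05 and 90% power, by the Freedman method.

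- HR = ln(1 − 0.0534)/ln(1 − 0.089) = 0.589, which gives 157 events.
- 157/(0.089 + 0.0534) = 1102.5 per arm, against 1102 stated.
- 1102/(1 − 0.15) = 1296.5, so 1297 per arm and 2594 in total, as stated.

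Masking changes none of these.

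**Heart failure alone: inputs.** The Background says that "the incidence of heart failure after acute myocardial infarction during hospitalization ranged from 40.2 to 40.5" per cent. This is a literature rate, not the trial's own expectation. I take p = 0.402 in both arms, so there is no true effect, and n = 1297 per arm. The fraction r of diagnoses that go unrecorded in the probiotic arm only is an assumption: 5% or 10%.

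**Difference that reaches p<0.05.** 1.96 × √(2 × 0.402 × 0.598/1297) = 0.0377, or 3.8 percentage points.

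**Chance of a false probiotic benefit.** With q = p(1 − r), d = p − q and p̄ = (p + q)/2:

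P = 1 − Φ[(1.96·s0 − d)/s1], where s0 = √(2p̄(1 − p̄)/n) and s1 = √([p(1 − p) + q(1 − q)]/n).

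- r = 5%: q = 0.3819, d = 0.0201, s0 = s1 = 0.0192. P = 1 − Φ(0.91) = 18%.
- r = 10%: q = 0.3618, d = 0.0402, s0 = s1 = 0.0191. P = 1 − Φ(−0.15) = 56%.
- With 1102 per arm, the figures are 16% and 49%.
- Without differential recording, the chance in that direction is 2.5%.
- At the 0.022 level that the interim plan sets for each analysis, the figures for 1297 per arm are about 11% and 43%.

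**Why these are not MACE figures.** A patient whose heart failure goes unrecorded may still count through another component. The documents give no MACE rate. If MACE were 50% and one third of the unrecorded patients still counted (both assumed), the shift would be 0.402 × r × 2/3, or 1.3 and 2.7 points. The chances would then fall to about 10% and 28%.

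**LVEF.** The documents give no standard deviation. With an assumed SD of 8 to 12 points and 1102 per arm, the standard error of a difference in means is SD × √(2/1102), or 0.34 to 0.51. An assumed reading shift of 0.5 point between arms gives p<0.05 in 16% to 31% of trials with no true effect; a shift of 1 point gives 50% to 84%. Masked reading would remove this kind of shift.

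**The case against.** **The main conclusion is hardly touched.** The primary outcome is all-cause death, which leaves an assessor little room for judgement, and the sample size rests on it. This stands and limits the point to the secondary outcomes.

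**Masking does not reach the modelled harm.** The 18% and 56% describe diagnoses missing from the record in one arm. That would happen at the bedside, among staff who must know the allocation, and later classification cannot recover signs that nobody wrote down. This stands: the figures show how sensitive the test is to differential recording, not how much masking would save.

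**Part of the heart-failure definition is objective.** Two of the four criteria are chest X-ray and natriuretic peptide. This stands in part: they narrow the room for judgement, but the definition does not say that either is required.

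**Analysts have little left to choose.** A reader might infer that unblinded analysts could pick covariates, exclusions and missing-data handling knowing the arm. The statistical section does not support that: it fixes an intention-to-treat population, predictive mean matching, and a chi-square test for the primary outcome and the secondary event rates, with no covariates in that test. Some imputation detail remains open, so coding the arms is still sensible, but the gain is modest.

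**Intent and cost.** A reader might also infer that assessors were left unblinded on purpose and that masking them would be free. The documents give no rationale beyond the open-label design, and no staffing or cost. They do not describe separate echocardiogram readers or event coders, so a second clinician to classify events cannot be assumed to be available.

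**Conclusion.** The point holds for the secondary outcomes. Unblinded assessment and analysis are stated outright rather than left to another document, and the lack of a placebo accounts only for patients and treating clinicians. LVEF, heart failure and cardiac death are therefore open to assessment bias that could partly be avoided.

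For heart failure alone, differential recording of 2 to 4 percentage points would raise the chance of a false benefit from 2.5% to about 18% to 56%. This rests on a literature rate of 40.2%, 1297 per arm and assumed under-recording in one arm only; nothing in the documents shows that such under-recording will occur. It should not be read as a prediction for MACE, where overlap between components would dilute it, nor as a threat to the mortality result.

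Masking would protect LVEF reading well, event classification in part and analysis modestly. Bias at the bedside would remain. The change is worth making because it is small and leaves treatment and sample size unchanged.

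**What to change.** Amend the Blinding section to say that:

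- patients and treating clinicians are not blinded;
- echocardiograms are read without the arm shown;
- analysts work with arms coded A/B until the analysis is locked, while the independent unblinded statistical centre already planned continues to support the interim reviews;
- where existing staff allow, heart failure and cause of death are classified from records with the allocation and study medication removed;
- bias in what is recorded at the bedside remains, and MACE will be interpreted with that in mind.

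The cost is administrative work to remove the arm from studies and extracts, and an amendment, which the protocol says needs ethics and regulatory approval before implementation. Recruitment began in October 2020 and is continuing, so the amendment must also say how patients already assessed unmasked are handled: for example, by re-reading stored echocardiograms where available, or by reporting the unmasked period. Classification by clinicians not treating the patient may need an extra assessor. If none is available, masked echocardiogram reading and coded arms are still worth having on their own.

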### Outcome measurements

Hospitalized patients will be followed daily until the occurrence of a primary end-point event or discharge from the hospital. Telephone follow-up will be conducted on the 30th day after admission to understand the survival status of the patients. For patients who have been hospitalized for more than 30 days, end-point events will be collected on day 30 of hospitalization.

#### Primary outcome

The primary outcome will be in-hospital all-cause mortality at 30 days. We will keep track of each patient’s survival through telephone follow-up and the electronic medical record system, and in case of death, the cause of death will be recorded. At the end of the trial, the total number of participants, the number and proportion of deaths in the two groups will be counted, and the in-hospital mortality will be compared between the two groups.

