**Methods:**

This is an open-label, randomized, controlled, superiority clinical trial involving 2594 adult patients who were diagnosed with acute myocardial infarction. Patients will be randomized to (1) receive bifidobacteria triple viable capsule (*Bifidobacterium longum*, *Lactobacillus acidophilu*s, and *Enterococcus faecalis*) 840 mg, twice a day, plus standard treatment strategy during the hospital stay, for a maximum of 30 days, or (2) receive the standard treatment strategy and will not take the bifidobacterium triple live capsule. The primary outcome was in-hospital all-cause mortality.

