### Study hypothesis and objectives

Studies have shown that patients with AMI have certain intestinal flora disorder and impaired intestinal barrier function [8]. When myocardial infarction occurs, intestinal bacteria and metabolites translocate into the systemic circulation, causing metabolic endotoxemia and stimulating systemic low-grade inflammation, thereby affecting the repair of the heart after myocardial infarction and the occurrence of adverse time after myocardial infarction [13]. Therefore, we hypothesized that early probiotic supplementation after AMI could have a positive effect on the heart by repairing the gut barrier, reducing endotoxemia and systemic inflammation.

The primary objective of this trial is to determine the effect of probiotics on in-hospital mortality of AMI patients. The secondary objective is to investigate whether probiotics can reduce the incidence of major adverse cardiovascular events (including heart failure, malignant arrhythmias, cardiogenic shock, myocardial infarction-related mechanical complications, and recurrent myocardial infarction) and improve ventricular systolic function in patients with AMI; echocardiography will be measured at baseline and after treatment.

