### Statistical and analytical plans

The analyses will adhere to intention-to-treat (ITT) principles. The ITT population included eligible patients who had been randomly assigned to participate in the study, regardless of whether any patients were taking a trial drug. Missing observations are accounted for using the predictive mean matching (PMM) method. Descriptive statistics will be used to analyze the results. Continuous data, such as age, height, and weight, will be presented as mean ± SD. Categorical data such as all-cause death, previous disease history, and smoking history will be expressed as frequency and percentage of patients in each category. Comparison baselines will be obtained using an independent sample *t* test. For the primary outcome, the chi-square test will be used to compare the all-cause mortality in both arms. Secondary outcomes will be assessed by the chi-square test for event rate, and the paired *T* test for quantitative secondary endpoints to compare both treatment arms. In addition, Kaplan–Meier curves will be calculated for visualizing the cumulative events in both groups during hospitalization. A *p*-value of less than 0.05 (*p* < 0.05) will be considered statistically significant. SPSS (25.0) will be used for statistical analysis.

The efficacy and safety of probiotics in the treatment of acute myocardial infarction are unknown. The purpose of interim analyses is to enable early detection of trial safety, early detection and termination of the study in the event of safety problems, and early detection of efficacy, which can be halted for efficacy if the trial is effective and has satisfied prespecified criteria. For interim analysis, we will do a group sequential statistical design with 2 interim analysis when we collect 33% (856) and 67% (1815) of the analyzable patients. The interim analysis will be performed using the Pocock method. Each analysis, including the final analysis, will be set at the same significance level alpha = 0.022 to maintain an overall significance level of 0.05. An independent Data Monitoring Committee supported by an independent, unblinded statistical center will regularly review safety data as well as the interim efficacy analysis.

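### The primary outcome does not say whether a death after discharge but before day 30 counts; on its plain reading it does not, so unblinded discharge decisions set the counting window

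*Protocol article*

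**What the plan says.** The Primary outcome section defines the endpoint: "The primary outcome will be in-hospital all-cause mortality at 30 days". It then says that each patient's "survival through telephone follow-up and the electronic medical record system" will be tracked, and closes with the comparison itself: "the in-hospital mortality will be compared between the two groups".

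Elsewhere the 30-day term is absent. The abstract has "The primary outcome was in-hospital all-cause mortality", and the objectives section has "The primary objective of this trial is to determine the effect of probiotics on in-hospital mortality of AMI patients". The Sample size section takes 8.9% as the mortality during hospitalization.

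On follow-up, the Outcome measurements section says: "Hospitalized patients will be followed daily until the occurrence of a primary end-point event or discharge from the hospital". It adds: "Telephone follow-up will be conducted on the 30th day after admission to understand the survival status of the patients". For stays beyond 30 days, endpoints are taken at day 30. The Follow-up section gives an average stay of 10 days. It schedules a day-30 contact, by phone or in person, for everyone who leaves earlier, and records readmissions. The Blinding section states that no party is blinded, including caregivers, outcome assessors and data analysts.

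**The concern.** There are two linked problems.

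**The count is not single-valued.** A telephone call on day 30 is not needed to count deaths on the ward, so listing it under the primary outcome suggests 30-day mortality. The closing comparison, the abstract and the objective point to in-hospital death. A death at home on day 12, or during a readmission on day 20, is assigned by neither. Two analysts could count different deaths from one database, in a trial with unblinded analysts and two interim efficacy looks.

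**On the plain reading, a decision made after randomisation sets the window.** For a patient with the average stay, 30 − 10 = 20 of the 30 days lie after discharge. All-cause death is objective, but whether it happens in hospital depends on when the patient leaves, and staff who know the allocation decide that. If the arms differ in how many deaths fall after discharge, the primary comparison moves although survival does not.

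**Working it through.** **1. The plan's own figure.** The inputs are in the Sample size section: 8.9% vs 5.34%, two-sided 0.05, 90% power, log-rank with Freedman's method, 15% dropout.
- HR = ln(1 − 0.0534)/ln(1 − 0.089) = 0.589.
- Events = (1.960 + 1.282)² × [(1 + HR)/(1 − HR)]² = 156.8, rounded up to 157.
- Per arm: 157/(0.089 + 0.0534) = 1102.5, against 1102 stated.
- Dropout: 1102/0.85 = 1296.5, so 1297 per arm and 2594 in total, as stated.

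The stated size reproduces. It rests on an in-hospital rate.

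**2. How unequal discharge could move the result (assumed figures).** The documents give neither a 30-day rate nor a post-discharge death rate. Assume true 30-day mortality of 8.9% in both arms, n = 1297 per arm, and let only the share of deaths before discharge differ (f_C control, f_T probiotic).
- Counted rates: p_C = 0.089·f_C, p_T = 0.089·f_T; apparent RR = p_T/p_C.
- Rejection probability = Φ[(d − z·s0)/s1] + Φ[(−d − z·s0)/s1], where d = p_C − p_T, s0 is the pooled and s1 the unpooled standard error. z = 1.960 for alpha 0.05 and 2.290 for 0.022, the plan's per-analysis level. Each figure is for one test, not for the three-look procedure.

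Example, 90% vs 80%: p_C = 0.0801, p_T = 0.0712, d = 0.0089, s0 ≈ s1 ≈ 0.01038. At 0.022 the two terms are Φ(−1.433) = 0.0759 and Φ(−3.148) = 0.0008, together 0.0767.

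| Share before discharge (control vs probiotic) | Counted rates | Apparent RR | False positives at 0.022 | at 0.05 |
|---|---|---|---|---|
| 95% vs 95% | 8.45% vs 8.45% | 1.00 | 2.2% | 5.0% |
| 95% vs 90% | 8.45% vs 8.01% | 0.95 | 3.4% | 7.0% |
| 90% vs 80% | 8.01% vs 7.12% | 0.89 | 7.7% | 13.7% |
| 90% vs 70% | 8.01% vs 6.23% | 0.78 | 29.9% | 42.2% |

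**3. What a 30-day count does to power (assumed figures).** Keep the planned in-hospital difference of 8.9 − 5.34 = 3.56 points and add post-discharge deaths that treatment does not affect. The setting is 1297 evaluable per arm, two-sided 0.05, single test.

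| Extra post-discharge deaths, both arms | Rates | Power | n per arm for 90% |
|---|---|---|---|
| 0 | 8.9% vs 5.34% | 94.2% | 1095 |
| 0.5% | 9.4% vs 5.84% | 92.8% | 1166 |
| 1% | 9.9% vs 6.34% | 91.3% | 1236 |
| 2% | 10.9% vs 7.34% | 88.3% | 1373 |
| 3% | 11.9% vs 8.34% | 85.3% | 1507 |

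If the 40% relative reduction instead held to day 30 with a control rate of 9.5% to 12%, 1020 down to 790 per arm would be enough.

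**The case against.** The strongest defence is that the endpoint is coherent as in-hospital death capped at day 30. The rule for stays beyond 30 days supplies the cap, and title, abstract, objective and sample-size rate all say in-hospital. Treatment too is given only in hospital, for at most 30 days. On this view, 30-day mortality is merely another design choice. The coherence stands as the most natural reading. It does not settle how readmission deaths count or why telephone follow-up is a source, and it leaves the window to the discharge decision, which also ends treatment.

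Several limits stand:
- A reader might infer that the protocol excludes post-discharge deaths by rule. It does not say so; exclusion is the plain reading only.
- A reader might infer that the primary result is biased. The documents show no difference in discharge between arms. Even a difference in length of stay is not enough by itself, because the share of deaths after discharge must differ.
- Twenty of 30 days is a share of time, not of deaths. The Discussion calls the initial stage after infarction critical for survival, so far fewer than two thirds of deaths may be missed.
- It is tempting to add that the survival curves, "Kaplan–Meier curves will be calculated for visualizing the cumulative events in both groups during hospitalization", are distorted by censoring at discharge. That censoring is inferred, the curves are descriptive, and the primary chi-square test does not use them.
- Changing the primary outcome of a recruiting open-label trial is more than a wording edit, and in-hospital death is easier to observe completely than vital status after discharge.

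**Conclusion.** The point holds as an ambiguity in the primary outcome, whose plain reading ties the counting window to unblinded discharge decisions. It should be fixed. The evidence does not support calling it a demonstrated bias.

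The possible distortion runs from none (equal shares) through slight (95% vs 90%: 3.4% against 2.2%) to serious (90% vs 70%: about 30%). These figures rest on an assumed 8.9% 30-day mortality, which the protocol gives as a hospital rate, on assumed shares, and on all 1297 per arm being analysed. The sample-size arithmetic is not in error, but it refers to in-hospital death and would need restating for a 30-day outcome.

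**What to change.** 1. Define the primary outcome as death from any cause by day 30, wherever it occurs, in all randomised patients. State that deaths at home and in readmissions count.
2. State one time origin and match the call to it. The call is now timed from admission, while patients have up to 24 h to consider consent and are randomised after signing. If randomisation is the origin, the call must move accordingly.
3. Keep in-hospital death as a secondary outcome, and align the title, abstract, objective and the closing comparison of the Primary outcome section.
4. Run any Kaplan–Meier curve for mortality to day 30. This is a minor, descriptive point.
5. Restate power for an assumed 30-day rate. Under the assumptions above it is about 93% to 85% for 0.5% to 3% extra unaffected deaths, at 1297 per arm and alpha 0.05.

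Cost: a dated amendment to the primary outcome of a recruiting open-label trial, possibly slightly lower power, and reliance on reaching discharged patients. The day-30 contact is already scheduled, so little or no extra data collection is needed beyond any shift in its timing. The change should be made before the next unblinded look; a later choice of which deaths count would be hard to defend.
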